## Background

The fetal intestine is (virtually) sterile, however, from birth onwards, the infant intestine becomes colonized with a wide variety of microorganisms [1]. The interaction between the host and its microbiota contributes fundamentally to overall health [2, 3]. For example, the microbial ecosystem provides the host with valuable metabolic features, such as metabolism of otherwise indigestible carbohydrates, xenobiotic metabolism, and production of essential metabolites such as vitamin K [4, 5]. Furthermore, the colonizing microorganisms play a key role in driving post-natal maturation of the infant gut and development of the mucosal immune system [6–10].

Disturbance of the microbial colonization patterns early in life can lead to long-lasting host effects and eventually disease. Aberrancies in microbial colonization patterns or distortion of the microbial ecology early in life might predispose the infant to the development of immune-mediated diseases. The gut microbiota has been associated with T-helper 2 (Th2) type diseases like allergy, wheezing and asthma, and also with T-helper 1 (Th1) type diseases, like inflammatory bowel disease, diabetes and obesity [11–24]. Also in non-immune mediated diseases, like infantile colic or irritable bowel syndrome, the fecal microbiota composition was found to be different from healthy controls [25, 26].

A range of factors can influence the composition of the intestinal microbiota and its establishment, like mode of delivery, feeding mode, contact with parents, siblings, and nursing and/or hospital staff when appropriate [27–29]. Antibiotic treatment during the early postnatal period, that has become common in modern obstetric and neonatal practice [15], is one of the important factors that can influence maturation of the infant gut microbiota and thus increase the risk of disease [11, 24]. A systematic review in 2011 of longitudinal studies on the effects of infant antibiotic use showed a higher risk for subsequent development of wheezing and/or asthma [30]. Other studies have shown an association between infant antibiotic exposure and growth rate and development of adiposity [31–33].

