## Methods/Design

### Study design and population

A prospective, observational cohort study with a one-year follow-up is currently conducted to determine the clinical effects and impact on the gut microbiota composition of empiric antibiotic use in early life. Infants are recruited from the maternity wards and neonatal wards of four teaching hospitals in the Netherlands: the St. Antonius Hospital in Nieuwegein, the Tergooi Hospital in Blaricum, the Gelre Hospitals in Apeldoorn and the Meander Medical Center in Amersfoort. This study was approved by the joined Medical Ethics Committee (VCMO) of the St Antonius Hospital and Meander Medical Center (nowadays MEC-U: Medical Research Ethics Committees United (Nieuwegein)). In The Netherlands, since 2013 studies only need to be approved by one Ethics Committee. Subsequently, for other participating centers, proof of local feasibility needs to be given. The approved protocol was consequently checked for local feasibility and expertise at Tergooi Hospital and Gelre Hospitals and permission for study implementation was obtained by the respective boards of directors. The study is performed in accordance with the ethical standards laid down in the 1964 Declaration of Helsinki and its later amendments.

All parents of term infants (≥ 36 weeks of gestational age) who stay in the hospital for at least 24 h, are approached for participation in the study.

In total 150 infants, treated with antibiotics because of (a high suspicion of) a perinatal infection during the first week of life, will be recruited. The control group comprises 300 healthy newborns, born in the hospital and needing clinical observation for 24–48 h for several reasons like maternal comorbidity, low probability of neonatal infection, blood sugar monitoring, meconium containing amniotic fluid, or delivery by caesarean section. For a balanced composition of the control group, as much as possible infants that are suspected to have a neonatal infection but for whom watchful waiting is allowed (and no antibiotic treatment has to be started) will be included.

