### Aims

Healthy newborns born in the hospital, observed for low probability of neonatal infection will be compared to newborns exposed to antibiotic therapy in early life (first 1–2 weeks) by investigating potential differences in fecal microbiota composition. For this purpose fecal bacterial composition and diversity is determined at eight time points during the first year of life, from birth on: day one (T1), day two (T2), one week (T3), two weeks (T4), one month (T5), three months (T6), six months (T7), one year (T8). An overview of the sample time points and outcomes is shown in Fig. 1.

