**Fig. 1 Fig1:**
[figure not shown]
Overview of the sample time points and outcomes

Potential differences in proportions (abundance and diversity) of intestinal bacterial groups (phyla) and species in antibiotic treated infants versus healthy controls will be determined by use of 16S-23S rRNA gene analysis. Secondly, we investigate differences in clinical outcomes between infants treated with antibiotics and controls. We evaluate incidences of atopic dermatitis (eczema), food allergy, upper respiratory tract infections (URTI), lower respiratory tract infections (LRTI), gastrointestinal infections (GITI) and excessive crying, prospectively assessed by parental reports and retrospectively assessed by doctor’s diagnoses. The clinical endpoints will be linked to the developing intestinal microbiota during the first year of life. Body mass index and standard deviation (SD)-scores are calculated from individual weight and height curves.

Parents of all included infants will report the use of antibiotics (type of antibiotics and duration of treatment) during the complete study period (i.e. the first year of life) on the calendar lists. Moreover, (the type of) prescribed antibiotics will be investigated at the end of the initial study period by approaching the infant’s pharmacy on medications used in the first year of life. Parents are also asked to report the moment of stool collection (date) on the collection vial, so the investigators can calculate the time between antibiotic treatment and stool sample collection. We hypothesize that in early life antibiotic treated infants develop more eczema during their first year than non-antibiotic treated infants (healthy controls). We also expect an increase in incidence of (parental reported as well as doctor’s diagnosed) food allergy, respiratory tract infections (RTI’s) and gastrointestinal tract infections (GITI’s) in infants treated with antibiotics compared to controls.

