### Statistical analysis

We will evaluate the potential relationships between antibiotic use in early life and the various (clinical) endpoints. Variables are verified for normal distribution and *t*-tests will be used for testing the null hypothesis. Either logistic regression analysis or cox regression analysis will be applied to the data (appearance of the primary endpoint(s) will be recorded as specifically as possible), so that odds ratios or hazard ratios and their 95 % confidence interval can be presented for description of the relationships. Multivariate models will be used to assess confounders and confounding effects. We will perform post hoc analyses to look for potential effects of the different antibiotic regimes. Outcomes may, possibly, be classified into subgroups. According to antibiotic treatment after the first two weeks, children will be grouped based on the number of antibiotic courses during the first year of life (0 / 1 / 2 or more courses). Within the ‘treatment groups’ a distinction can be made between the class or spectrum of the prescribed antibiotics.

Microbiota composition will be described by means of abundance, diversity and (dis)similarity. Diversity is calculated using the Shannon index [42] and differences in this index will be tested with Mann–Whitney *U* test. Dissimilarities between samples, or between-sample diversity, are calculated as the cosine distance between each pair of samples and analyzed with principal coordinate analysis (PCoA). All statistical analysis will be conducted using SPSS version 22.0 (SPSS Inc., Chicago, IL, USA) and the vegan software package in R (Foundation for Statistical Computing, Vienna, Austria).

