## Discussion

To the best of our knowledge, this is the first prospective observational cohort study, with a follow-up of one year, addressing clinical outcomes after empiric antibiotic treatment in early life which at the same time investigates the development of intestinal microbiota composition after this antibiotic exposure. Subsequently, extensive clinical outcomes can be linked to microbiota composition over time. This study includes a total of 450 infants, of whom 150 are exposed to antibiotic treatment shortly after birth and 300 controls. Previous studies addressing consequences of antibiotic treatment in early life were hampered by a retrospective approach [11, 33, 39, 47], divergent study populations [48], smaller sample sizes [17] or a limited period of follow-up [34, 49].

By assessing an extended number of clinical parameters in a fairly large group, and subsequently strictly selected homogeneous subgroups of infants, bias due to confounding factors such as mode of delivery and type of feeding is expected to be reduced. Results from this study may improve our understanding of the evolving microbiota in term infants. Also, by collecting fecal samples at eight time points during the first year of life and around the second birthday, long-term microbiota development can be investigated.

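### The only group test named for the microbiota aim is an unadjusted Mann-Whitney test of diversity, which cannot separate antibiotic exposure from delivery mode or use the repeated samples per infant

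*Protocol article*

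**What the plan says.** The Aims section begins with the microbiota comparison between antibiotic-treated infants and controls, for which "fecal bacterial composition and diversity is determined at eight time points during the first year of life". Clinical outcomes come after it: "Secondly, we investigate differences in clinical outcomes between infants treated with antibiotics and controls".

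The microbiota paragraph of the Statistical analysis section names one hypothesis test: "Diversity is calculated using the Shannon index [42] and differences in this index will be tested with" the Mann-Whitney U test. Between-sample dissimilarity is computed as cosine distance and analysed by principal coordinate analysis (PCoA). No test of group difference is named for it.

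Three other places bear on confounding:

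- Background: "A range of factors can influence the composition of the intestinal microbiota and its establishment, like mode of delivery, feeding mode".
- Study design and population: the reasons for observing a control infant include "blood sugar monitoring, meconium containing amniotic fluid, or delivery by caesarean section".
- Statistical analysis, in the separate paragraph on clinical endpoints, directly after the odds and hazard ratios: "Multivariate models will be used to assess confounders and confounding effects".

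The Discussion adds an expectation that, through "strictly selected homogeneous subgroups of infants, bias due to confounding factors such as mode of delivery and type of feeding is expected to be reduced".

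**The concern.** Controls and treated infants enter by different routes. Treated infants enter because of suspected or proven perinatal infection. Controls enter because they need short observation, and caesarean birth is one such reason. If caesarean shares differ between the groups and delivery mode affects diversity, an unadjusted two-sample test measures antibiotic exposure and delivery mode together. The imbalance could produce a difference when antibiotics have no effect, or hide a real effect.

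The test also does not fit the sampling scheme. A two-sample rank test uses one value per infant. Run at each time point it is valid, but it ignores the within-infant information that eight samples provide. Run on pooled samples it would treat repeated samples from one infant as independent. The article does not say which is meant.

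At stake is whether the result for the first-listed aim can be attributed to antibiotics.

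**Working it through.** **Does the stated text supply adjustment for diversity?**

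1. The Mann-Whitney test has no covariate term, so the test itself cannot adjust.
2. The multivariate models follow the odds and hazard ratios in the clinical-endpoint paragraph. The microbiota paragraph, which is separate, does not mention them.
3. The homogeneous subgroups appear only in the Discussion. They are not defined and no analysis is attached to them.

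Nothing in the article ties adjustment or restriction to the diversity comparison.

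**How much could it matter?** The article gives no figure for the diversity test, so there is none to reproduce. What follows is an illustration.

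Inputs from the article:
- Group sizes: 150 and 300, less 15% dropout. 150 × 0.85 = 127.5, taken as 127; 300 × 0.85 = 255.
- Significance level: 5%. It is stated for eczema and borrowed here, two-sided.

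Assumed inputs:
- No antibiotic effect.
- A gap in caesarean share between the groups of 10, 20 or 30 percentage points.
- A delivery-mode effect on the Shannon index of 0.3, 0.5 or 0.8 SD.
- One time point, one sample per infant.

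Formulas:
- Bias in SD units = gap × delivery effect.
- Standard error = √(1/127 + 1/255) = 0.1086.
- Shift in z = 0.977 × bias / 0.1086, where 0.977 = √(3/π) reflects the efficiency of the Mann-Whitney test under normality.
- Rejection rate = Φ(−1.96 + shift) + Φ(−1.96 − shift).

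Example: a 20-point gap and 0.5 SD give a bias of 0.2 × 0.5 = 0.10 SD, a shift of 0.977 × 0.10 / 0.1086 = 0.90, and a rejection rate of 14.7%.

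The formula was checked by simulating Mann-Whitney tests (4,000 replicates per cell, caesarean share 20% in treated infants and higher in controls by the gap).

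| Gap | Delivery effect | Bias (SD) | Formula | Simulation |
|---|---|---|---|---|
| 10 points | 0.3 SD | 0.03 | 5.8% | 5.4% |
| 10 points | 0.5 SD | 0.05 | 7.4% | 6.8% |
| 10 points | 0.8 SD | 0.08 | 11.1% | 10.6% |
| 20 points | 0.3 SD | 0.06 | 8.4% | 8.4% |
| 20 points | 0.5 SD | 0.10 | 14.7% | 14.3% |
| 20 points | 0.8 SD | 0.16 | 30.2% | 28.0% |
| 30 points | 0.3 SD | 0.09 | 12.8% | 12.5% |
| 30 points | 0.5 SD | 0.15 | 27.1% | 25.2% |
| 30 points | 0.8 SD | 0.24 | 57.9% | 54.9% |

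The simulation runs slightly lower because mixing delivery modes within a group widens the spread, which the formula ignores. Taking both methods together, the ranges are about 5-11%, 8-30% and 12-58%.

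**The case against.** The strongest reply is that the article does recognise the problem. It announces multivariate models and names delivery mode and feeding as confounders that homogeneous subgroups should reduce. It seeks controls with suspected infection under watchful waiting, and it concedes non-comparability of the groups as a main limitation. A Mann-Whitney test within delivery-mode strata would handle delivery mode by restriction. Moreover, the microbiota is to be described, the sample size rests on eczema, and no alpha is attached to diversity. This softens the point: the authors may intend more than the microbiota paragraph says. It does not remove it, because neither the models nor the subgroups are linked to the one test that is named. Seeking watchful-waiting controls addresses the indication for treatment, not delivery mode.

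Three stronger readings are tempting, and the article supports none of them:

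- **Uncontrolled multiplicity over eight tests.** A reader might infer eight separate tests at 5%, with a familywise error of 1 − 0.95⁸ = 34% if independent. The article does not say that the test is run at each time point, or that results go uncorrected. Such detail is commonly left to a full protocol or analysis plan, which is not shown.
- **A control group known to be enriched for caesarean births.** Caesarean section is the last of several example reasons for observation. No share is given for either group, and treated infants may also be born by caesarean.
- **A deliberate decision not to test dissimilarity.** The article names PCoA and the vegan package. It names no group test, but does not rule one out.

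**Conclusion.** The point holds for confounding and for the fit of the test to the design. As written, the first-listed aim rests on an unadjusted two-sample test, while the article itself identifies delivery mode and feeding as influences on the outcome and lists caesarean section as a route by which controls enter. A difference in diversity, or the lack of one, could not be attributed to antibiotics on that test alone.

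The size is conditional. With a 10-point gap in caesarean share the false-positive rate stays between nominal and about 11%. The rate near 58% belongs only to the most extreme assumed case. Neither the gap nor the delivery effect comes from the article, and the bias could run in either direction. The case for change rests on the method being unable to correct an imbalance that the recruitment rule makes plausible, not on an imbalance that has been shown.

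**What to change.** Make the main diversity analysis a linear mixed model of the Shannon index on exposure, time and exposure × time, with a random infant effect, adjusted for delivery mode, maternal peripartum antibiotics, gestational age and hospital. Delivery data and maternal antibiotics are recorded (Inclusion and exclusion criteria), gestational age is in the baseline questionnaire (Outcomes), and hospital is known from recruitment.

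Two limits should be written in:

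- **Feeding.** Parents report it monthly, so feeding status at the day 1, day 2, one-week and two-week samples is not documented as recorded. Add reported feeding in a sensitivity model where it is available.
- **Timing.** Treatment falls in the first week by one section and the first one to two weeks by the Aims, so the earliest samples may precede or coincide with it. Base the antibiotic effect on samples taken after treatment start, and use earlier samples to check baseline comparability. A joint exposure test over all eight points could mix pre-exposure differences into the effect. Controls have no start date, so state which time points count for them. Dates on the vials let the interval from treatment be calculated.

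Test cosine distances by PERMANOVA in vegan, which is already named, with the same covariates, and keep PCoA for display. If the subgroups in the Discussion are meant to serve the microbiota analysis, define them there.

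The cost is analysis wording, a little more analysis work and checks of model residuals. No new samples or visits are needed.

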### Data analysis

After pre-processing (IS-pro software suite, IS-Diagnostics), each sample is represented by a microbial profile, consisting of color-labelled peaks. Each peak is characterized by a specific IS fragment (measured as nucleotide length) and a color related to a specific phylum group. The intensity of peaks reflects the relative quantity of PCR product (measured in relative fluorescent units). We further consider each peak as an operational taxonomic unit (OTU) and its corresponding intensity as relative abundance. Intensity values are log2 transformed when appropriate in order to compact the range of variation in peak heights, to reduce the dominance of abundant peaks and include less abundant species of the microbiota in downstream analyses and more related to the in vivo situation. This transformation results in improved consistency of the estimated correlation coefficient, lower impact of inter-run variation, and improved detection of less prominent species. This conversion is used in all downstream analyses, such as calculating within-sample and between-sample microbial diversity [41].

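### The analysis named for the cosine distances is an ordination, which cannot test the antibiotic-versus-control difference in composition that is the first aim

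*Protocol article*

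**What the plan says.** All places are in the protocol article.

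- **Aims.** Treated and control newborns are to be compared on microbiota composition, and "fecal bacterial composition and diversity is determined at eight time points during the first year of life". The same section adds: "Potential differences in proportions (abundance and diversity) of intestinal bacterial groups (phyla) and species in antibiotic treated infants versus healthy controls will be determined". Clinical outcomes come second in that section.
- **Statistical analysis, microbiota paragraph.** "Microbiota composition will be described by means of abundance, diversity and (dis)similarity". For one of these measures a group test is named: "Diversity is calculated using the Shannon index [42] and differences in this index will be tested with" the Mann–Whitney U test. For dissimilarity the next sentence says: "Dissimilarities between samples, or between-sample diversity, are calculated as the cosine distance between each pair of samples and analyzed with principal coordinate analysis (PCoA". The Abstract repeats this.
- **Software.** SPSS and "the vegan software package in R" are named, without a function or a test.
- **Background.** Delivery mode and feeding mode are listed among the influences on the infant microbiota.
- **Study design and population.** Caesarean delivery is one of the reasons for the short hospital stay that makes an infant eligible as a control. Recruitment is at four hospitals, with 150 treated infants and 300 controls.
- **Discussion.** The difference between sick, treated infants and healthy controls is called one of the main limitations. The two separate PCRs are said to hamper direct comparison of relative abundance across the three phyla together.

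**The concern.** The cosine distance is the only measure in the plan that summarises how far two samples differ in the taxa they contain. It is therefore the natural carrier of the first aim. The method attached to it projects the distance matrix onto a few axes for plotting. Group membership plays no part in that calculation, and neither does any covariate.

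At stake is what the study can say about its lead question. A plot with two partly separated clouds can be read as an antibiotic effect, and one with overlapping clouds as no effect, without an error rate or an effect size behind either reading. Because the study is not randomised, separation could also come from factors that differ between the groups. Delivery mode is a clear candidate, since caesarean section is itself a route into the control group.

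**Working it through.** The plan states no figure for this comparison (no expected distance, R-squared or alpha for the microbiota), so there is nothing to reproduce. The check sets each part of the aim against the method named for it.

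**1. Which stated method could answer the composition question?**

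| Measure | Method named | Group test? | Adjusts for confounders? | Reflects which taxa differ? |
|---|---|---|---|---|
| Shannon index | Mann–Whitney U | Yes | No | No |
| Cosine distance | PCoA | No | No | Yes |
| Phylum and species abundance | None named | – | – | Yes |

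No row has both a named group test and sensitivity to which taxa differ. No row has a named adjusted analysis.

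**2. Does the Shannon test fill the gap?** Take two taxa with shares (p, 1 − p) in one infant and (1 − p, p) in another.

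- The Shannon index is −p ln p − (1 − p) ln(1 − p) for both, so the difference is 0 for every p.
- The cosine distance is 1 − 2p(1 − p) / [p² + (1 − p)²]. It is 0 only at p = 1/2 and approaches 1 as p approaches 0 or 1.

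Two groups can thus agree exactly on Shannon and be almost as far apart as possible on cosine distance. A null Shannon result says nothing about the first aim's composition question, and a positive one does not show which composition changed.

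**3. Could the multivariate models in the same section apply?** They appear in the paragraph on clinical endpoints, next to logistic and Cox regression. PCoA has no place for a covariate, so they cannot adjust the analysis as named.

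**4. What would eight global tests cost in error rate?** This bears on the remedy. With one test per time point at 0.05 and no correction, the chance of at least one false positive is 1 − 0.95^8 = 0.337 if the tests are independent. The same infants are sampled repeatedly, so the tests are correlated and the true figure would be lower. Holm holds it at 0.05 or below under any correlation. Its thresholds run from 0.05/8 = 0.00625 for the smallest p-value to 0.05 for the largest.

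**The case against.** **This is a condensed article.** The full protocol and SAP are not shown, the exact distance-based test is often left to them, and vegan, which is named, can supply one. Part of this stands: the article does not show that no test is planned. But the section is not silent. It goes down to individual tests, including Mann–Whitney U for Shannon, and in the next sentence it names PCoA as the analysis of the distances. That is a stated choice, and it can be judged against the aim.

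**The wording is descriptive, and PCoA gives axis scores and variance explained that could be compared between groups.** The article does not say that this will be done. The variance explained by an axis is a share of all variation between samples, not the share due to antibiotics. And the aim is worded as a comparison between groups, not only as a description.

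**Confounding is handled elsewhere.** The Discussion expects homogeneous subgroups to reduce bias from delivery mode and feeding. Plotting subgroups might help, but it still gives no test, and the text does not tie the subgroups to this analysis.

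**A stronger reading is tempting.** The Data analysis section says "We further consider each peak as an operational taxonomic unit (OTU) and its corresponding intensity as relative abundance", and species differences are promised at eight time points. A reader might infer that every peak will be tested at an unadjusted 5% and that many false species findings are bound to follow. The document does not support this. It states no peak-wise test, no alpha for taxa and no number of peaks; its only alpha belongs to the eczema power calculation. Rules for multiplicity at taxon level are also what a condensed article commonly leaves to the full plan. Counts of expected false positives would therefore rest on assumptions throughout.

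**Conclusion.** The point holds in a narrow form. For the composition comparison that comes first among the aims, the article names an ordination as the analysis of between-sample dissimilarity. That method yields no test, no group effect size and no adjustment, and the Shannon test does not make up for it.

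The consequence is qualitative. The antibiotic effect on overall composition would rest on reading a plot, in groups that may differ in delivery mode, feeding and hospital. The document gives no basis for a numerical bias or error rate. The conclusion assumes only that the named method is the one that will be used. If the full plan already specifies an adjusted group test on the distances, what remains is to correct the sentence in the article.

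The change should be made, but the weight is moderate: the eczema endpoint and its sample size do not depend on it.

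**What to change.** Amend the sentence on dissimilarity in the Statistical analysis section:

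- Keep PCoA as the display.
- At each of the eight time points, test the group difference by permutational MANOVA on the cosine distances, using vegan. Antibiotic group is the tested term, assessed after delivery mode, feeding and hospital. Report R-squared and p.
- Apply Holm over the eight time points.
- Add a check of equal dispersion at each time point. The permutation test can respond to a difference in spread as well as in location, and this matters more with groups of 150 and 300. If spreads differ, say so beside the result.
- Because of the two separate PCRs, also report the test per phylum group, as support for the test on the whole profile.

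The cost is small: a few sentences and a few lines of code in software already named. No new data are needed, since delivery data, feeding type and recruiting hospital are already recorded. The downsides are slightly more analysis and the possibility that a separation visible on the plot is not confirmed after adjustment. Testing time points separately is simple but does not model each infant's course; a longitudinal model would be a reasonable alternative if fixed in advance.
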